## Abstract

**Background:**

Dysmenorrhea is a common menstrual complaint among adolescent girls and women of reproductive age. The treatment of dysmenorrhea is typically selected from multidisciplinary options, including complementary and alternative medicine such as acupuncture and moxibustion. However, there are few published randomized controlled trials concerning moxibustion treatment for dysmenorrhea. This trial aims to investigate the efficacy and safety of moxibustion for primary dysmenorrhea, and to identify the optimal time of moxibustion treatment for primary dysmenorrhea.

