**Discussion:**

This trial aims to assess the effectiveness and safety of moxibustion for primary dysmenorrhea, as well as to determine whether the optimal time of treatment for primary dysmenorrhea in clinical practice is before or after the onset of menstrual pain.

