#### Sample size

A previous study found that the mean on the Cox Menstrual Symptom Scale (CMSS) of PD patients after moxibustion was 1.62 [24]. The average CMSS values of subjects in the proposed study, with the square of standard deviation, are expected to be 1.7, 1.9, and 2.5 for patients treated with moxibustion before menstruation, those treated at the time of menstrual onset, and the waiting list group, respectively. In this case, the three groups are set with the ratio of 1:1:1 as the statistical power is 0.90 and the significance level is 0.05. The sample size was estimated by One Way ANOVA Power Analysis (11th edition, NCSS, LLC, Utah, United States) in NCSS-PASS (11th edition, NCSS, LLC, Utah, United States). After the estimation, the effect size is 0.2266 with 64 patients in each group and 192 patients in total. Therefore, there should ideally be 222 patients in total, with each group containing no less than 74 patients, estimating a dropout rate is 15%.

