#### Analysis

A statistician blinded to the whole trial process will perform the statistical analysis using the SAS statistical software package (Version 9.1, SAS Institute Inc.) in the Computer Integrated Manufacturing System. For the evaluation of curative effect in this trial, the per protocol set (PPS) will be used. The full analysis set (FAS) is determined according to an intention-to-treat population; all patients who are randomized and receive at least one treatment session will be included in the analysis set. The PPS is defined as the patients who complete the study and do not have major protocol violations. Demographic data and other basic indicators will be analyzed to test the balance of the three groups at baseline. The main indicators and global indicators will be analyzed within the FAS and PPS. The results will be described with the mean, standard deviation, median, P25 (Percentile 25), P75 (Percentile75), maximum, and minimum values of the differences between the treatment period and the baseline period. Between-group differences will be tested using repeated measure analyses of variance. The accepted level of significance for all analyses was *P* <0.05. Considering that the efficacy might be affected by factors such as age, age of menarche, and course of disease, all factors will be considered as co-variants for covariance analysis or logistic regression analysis when comparisons among groups are made. Missing data will be replaced according to the principle of multiple imputations.

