## Discussion

This proposed trial is a randomized, controlled clinical trial with separation of the practitioner, assessor, and statistician. The aims of this trial are to evaluate the efficacy and safety of moxibustion for treating PD, and to identify the optimal interventional time of moxibustion for PD treatment.

The form of moxibustion used in this trial will be suspended moxibustion treatment. When suspended moxibustion is applied to acupoints, the patient will have non-local or non-superficial heat sensation, such as penetrating heat, expanding heat, and transmitting heat, as *DeQi* appears. Selection of optimal acupoints for PD plays an important role in moxibustion treatment effectiveness. In practice, the treatment effect of moxibustion is affected by many other influential factors, including the intensity of heat stimulation, the ingredients of the moxa pillar, and the moxibustion sensations experienced. The most important factor contributing to the effectiveness of moxibustion is thought to be the selection of proper interventional time. However, in existing studies, interventional timing of moxibustion was not included as a key variant to be assessed.

In another undergoing study, we mainly focused on the effectiveness of moxibustion for pain relief in PD, which can be referred to the published protocol [32]. As to the current one, it is conceived on the basis of the former one. As indicated by the results from the initial analysis, moxibustion is effective for PD pain management; thus we want to further assess the impact of intervention time of moxibustion on the outcome of treating PD, so as the physiological tests’ change by treatment. In clinical practice, moxibustion treatment for PD can also be differed by the intervention timing in China, and there is no relative study on this focus. Thus we carried out the present study as a continuum which is reported by the current protocol. It is anticipated that the result may demonstrate the optimal interventional timing for PD and further extend our understanding of intervention from a chrono-therapeutic perspective, which will be highlights of our further reports. Moreover, the present study that was designed in accordance with the Consolidated Standards of Reporting Trials (CONSORT) statement, and guidelines will provide useful information to guide the clinical practice of moxibustion for PD.

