In addition, our study may also have the following strengths which will be potential points of discussion in the final reports. The dysmenorrhea diaries will be used to record the symptoms and management of menstrual pain in every menstrual cycle; these diaries are important for quality monitoring of the recurrence of new PD episodes. Besides the evident physical concerns, PD may be particularly disruptive to adolescent girls and women who experience mood fluctuations, such as depression or anxiety. There is increasing evidence that psychological disorders coexist with dysmenorrhea, and these conditions may synchronize with menstrual pain. The question remains whether anxiety and depression make women prone to suffering from dysmenorrhea, or whether dysmenorrhea causes anxiety and depression. We believe that women with mood changes tend to have lowered pain thresholds compared with mentally healthy women. Anxiety and depression disrupt patients’ experiences, expressions, behaviors, and pain-coping responses. Therefore, a better understanding of the relationship between psychological characteristics and PD is crucial to the assessment of the effectiveness of moxibustion as a treatment for PD. Hence, we will apply the SAS and the SDS to examine the link between PD and psychological symptoms of depression and anxiety among dysmenorrhea sufferers.

On the other hand, there are also limitations to this study. Concealment is the most critical factor in the allocation process, with a high risk of bias possibly generated by unconcealed allocation [33]. One limitation of this study is the possibility of a high risk of bias regarding blinding, as the waiting list group will be used as a control instead of a group receiving a sham procedure. Another limitation is that as moxibustion treatment will begin five to seven days before menstruation or at the onset of pain, the treatment may interfere with the menstrual period; treatment may cause menstruation to occur one or two days sooner or later than the usual cycle. Therefore, it may be difficult to predict an exact menstruation start date for the patients, and this may affect the therapeutic effect.

It is believed that this trial will provide good evidence to demonstrate the efficacy and safety of moxibustion for patients with PD. Moreover, it will be of great significance for clinical practice to identify an optimal moxibustion treatment time for PD.

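### The sample size is set for a three-group overall test that the waiting-list arm drives; the timing question, A versus B, has only about 12% power on a single measurement

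*Protocol article*

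**What the plan says.** The Abstract (Background) gives two aims: the efficacy and safety of moxibustion, and "to identify the optimal time of moxibustion treatment for primary dysmenorrhea". The Abstract (Discussion) puts the second as a two-way choice, to "determine whether the optimal time of treatment for primary dysmenorrhea in clinical practice is before or after the onset of menstrual pain". The Discussion section says that initial results of an earlier study already point to efficacy, "thus we want to further assess the impact of intervention time of moxibustion on the outcome of treating PD", and closes by saying that "it will be of great significance for clinical practice to identify an optimal moxibustion treatment time for PD".

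The Sample size section states: "The sample size was estimated by One Way ANOVA Power Analysis". The CMSS values "are expected to be 1.7, 1.9, and 2.5 for patients treated with moxibustion before menstruation, those treated at the time of menstrual onset"; the third mean, 2.5, belongs to group C. It also says that "the statistical power is 0.90 and the significance level is 0.05", and reports an effect size of 0.2266 with 64 patients per group (192 in total), raised to 74 per group (222 in total) for 15% dropout. No SD is printed.

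For the test, the Analysis section states: "Between-group differences will be tested using repeated measure analyses of variance". It uses P<0.05 throughout and foresees covariate adjustment when groups are compared.

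**The concern.** An overall F test over three groups can reject because the waiting list differs from both treated arms, whatever the relation between A and B. Its power therefore says little about the timing question. The planning means put A and B only 0.2 apart, while C lies 0.8 above A and 0.6 above B.

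If this holds, the likeliest result is a significant overall P value with an inconclusive A−B difference. A report could then name the arm with the lower mean as the optimal time, or conclude that timing does not matter. The data would support neither statement, yet the protocol presents the timing answer as guidance for practice.

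**Working it through.** **Inputs.** Means 1.7 (A), 1.9 (B) and 2.5 (C), f = 0.2266, 64 per group, alpha 0.05 and power 0.90, all from the Sample size section. Two-sided pairwise tests are assumed.

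**Step 1: the implied SD.** The grand mean is 2.033 and the squared deviations sum to 0.3467. The SD of the means is √(0.3467/3) = 0.3399, so the implied SD is 0.3399/0.2266 = 1.50.

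**Step 2: reproduce the plan's figure.** For a one-way ANOVA, λ = N·f² = 192 × 0.2266² = 9.86 with 2 and 189 degrees of freedom. Power is 80.3%. The smallest n per group for 80% is exactly 64; 90% needs 84. So f and n agree with each other at power 0.80, not at the stated 0.90. Taking 1.5 as the variance (SD 1.22) gives f = 0.278 and 93.7% power, which matches neither printed figure.

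**Step 3: what drives the overall test.**
- The A-versus-B share of the between-group sum of squares is (0.2²/2)/0.3467 = 5.8%.
- With A and B both set to 1.8 and C at 2.5, f = 0.220 and overall power is still 78%.

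**Step 4: pairwise power.** Two-sample t test, non-central t, 64 per group, SD 1.5:

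| Contrast | Difference | Power |
|---|---|---|
| A vs B | 0.2 | 11.6% |
| B vs C | 0.6 | 61% |
| A vs C | 0.8 | 85% |

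With all 74 per group retained, A vs B has 12.7%.

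**Step 5: precision.**
- The 95% CI half-width for A−B is 1.96 × 1.5 × √(2/64) = 0.52, against an expected 0.2.
- The smallest difference detectable with 80% power is (1.96 + 0.842) × 1.5 × √(2/64) = 0.74.
- For 80% power at 0.2, n = 2 × (1.96 + 0.842)² × (1.5/0.2)² = 883 per group.

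**Step 6: sensitivity of A-vs-B power.** One assumption is changed at a time; ranges cover 64 to 74 per group. The correlations are assumptions.
- SD 1.6 to 1.4: 11 to 14%. SD 1.22: 15 to 17%. SD 1.0: 20 to 23%.
- Mean of three cycles, within-person correlation 0.3 to 0.7: 13 to 20%.
- Mean of six cycles, same correlations: 14 to 24%.
- Baseline adjustment, correlation 0.3 to 0.7: 12 to 20%.

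Combining averaging with baseline adjustment goes somewhat higher. The residual SD is 1.5 × √((1 + (k−1)ρ)/k − ρ²). Three cycles with ρ = 0.5 give 0.968 and 21% at 64 per group. Six cycles with ρ = 0.7 give 0.765 and 31%.

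**Step 7: likely outcome.** In 40,000 simulated trials under the planning means (64 per group, SD 1.5), the overall test was significant and A−B was not in 69%. B had the lower mean, the wrong order, in 23%.

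**The case against.** Four points can be made for the plan.

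1. **A reader might infer that the plan allows only an overall test.** The document does not support that. A repeated-measures ANOVA supports an A−B contrast, and the Analysis section expects comparisons among groups. The contrasts and any multiplicity rule may stand in an SAP that is not shown, so their absence is not a defect here. This objection stands. It does not reach the sizing, which the protocol fixes: no contrast named later makes 64 to 74 per group adequate for a 0.2 difference.

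2. **The 12% is not the power of the planned analysis.** It is for a single measurement, and the SD is back-solved, not printed. That is right, and it is why a range is given. Some of the possible gain is doubtful: Table 2 schedules no CMSS before treatment, so a baseline covariate would have to be another measure. No scenario examined approaches adequate power.

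3. **Efficacy is listed first, and A versus C has 85% power.** This stands too. It would be wrong to infer that the trial can answer nothing. But timing is an aim in its own right, and the Discussion gives it as the reason for this study.

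4. **The trial need not be powered for every aim.** True, provided that the protocol says which aim the power covers and limits the claims on the other. It does neither.

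**Conclusion.** The point holds as a mismatch between the sample-size justification and the timing aim. On the plan's own means and the implied SD of 1.5, A versus B has about 12% power on one measurement. The range is roughly 11 to 24% when SD (1.0 to 1.6), cycle averaging or baseline adjustment is varied singly, and about 31% in the most favourable combination tried at 64 per group. The overall test has about 80% power, and 78% with no timing effect at all, so its significance carries almost no information on timing. The stated 0.90 does not follow from f = 0.2266 and 64 per group.

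The pairwise figures rest on the back-solved SD, two-sided 5% tests and the assumed 0.2 difference. A true A−B difference of about 0.74 would have 80% power, but that is more than three times what the plan expects.

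**What to change.** **Sample size section.** State that the power refers to the overall three-group test. Correct it from 0.90 to about 0.80 for f = 0.2266 and 64 per group, noting that 0.90 would need about 84. Print the SD. State that A versus B has only about 12 to 24% power at the assumed 0.2 difference, with the assumptions behind that range.

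**Analysis section.** Base the timing conclusion on the A−B contrast from the repeated-measures model. Test it only after a significant overall group effect, and say which group effect and which cycles that means. Report the difference with its 95% CI (half-width about 0.52 on a single measurement). Claim an optimal time only if that test is significant and the CI excludes 0. State that a non-significant difference will not be read as equivalence of the two timings.

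**Cost.** Wording only, with no extra patients. The timing claim and the stated power become more modest. Powering the timing aim itself at 0.2 would take about 883 per group, which is not proposed.

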#### Secondary outcome measurements

##### Visual Analogue Scale

The severity of menstrual pain will be measured with the VAS, a 100-mm horizontal line with endpoints from no pain on the far left to the worst possible pain on the far right. The VAS is scored by measuring in millimeters the distance from the side marked no pain to the edge of the mark made by the patient. Possible scores range from a minimum of 0 to a maximum of 100 mm, as participants will be asked to indicate a perception of pain intensity scored from one to 100. The VAS will be used during baseline measurements and during the first, second, third, fourth, fifth, and sixth menstrual cycle after inclusion.

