##### Self-rating Depression Scale

The Self-rating Depression Scale (SDS) is a 20-item self-reporting questionnaire on the symptoms of depression. Subjects rate each item according to how they felt during the preceding seven days. Item responses are ranked from one to four. The sum of the 20 items produces a score between 20 and 80, with a score of greater than 40 suggesting clinically relevant depression [30]. The SDS will be used on the day when menstruation ends in the last month of the baseline period, and in the fourth menstrual cycle after inclusion (after completion of three sessions of treatment).

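### The between-group analysis of VAS, SDS and SAS does not name the baseline value of the outcome as a covariate, although it is collected; adding it gains precision at no cost.

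*Protocol article*

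**What the plan says.** The Analysis section of the protocol article makes three statements that bear on this point.

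- **Description.** Results are summarised by means, SDs, percentiles and extremes, given as "values of the differences between the treatment period and the baseline period".
- **Test.** A separate sentence says that groups are compared by repeated-measures ANOVA. It does not say whether the response is the raw score or the change, or whether baseline enters as a time level.
- **Covariates.** Group comparisons are to allow for "factors such as age, age of menarche, and course of disease, all factors will be considered as co-variants for covariance analysis" or logistic regression. The three items are given as examples.

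The same section also uses baseline data to check that the groups are balanced.

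Pre-treatment values exist for three secondary outcomes. For pain: "The VAS will be used during baseline measurements and during the first, second, third, fourth, fifth, and sixth menstrual cycle after inclusion". For depression: "The SDS will be used on the day when menstruation ends in the last month of the baseline period", and once more after the three treatment cycles. The anxiety scale follows the same timing. For CMSS, the primary outcome, neither its own section nor Table 2 schedules a measurement before treatment.

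**The concern.** In a trial with repeated symptom scores, a patient's own baseline score is usually the best single predictor of her later score. The plan already intends a covariance analysis and names three patient characteristics for it, but not this one. If the model is run as written, part of the between-patient variation in VAS, SDS and SAS stays in the error term although data already collected could remove it. At stake is the width of the confidence intervals for the secondary outcomes, including VAS, the direct pain measure that supports the comparison of the two treatment timings.

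**Working it through.** The document gives no figure for the precision of these comparisons, so there is none to reproduce. The sample size calculation concerns CMSS and is not an input here.

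**Inputs from the document.** SDS and SAS: one value before and one after treatment. VAS: baseline, inclusion and each of six later cycles; the three treatment cycles are used below.

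**Assumptions, not in the document.** Equal SD before and after (set to 1); pre-post correlation r of 0.3, 0.5 or 0.7; for VAS, the same correlation between any two cycles. The number of baseline VAS scores is not clearly fixed, so both three and one are shown.

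**Step 1. Possible readings of the ANOVA.**
- Change scores: compared directly in Steps 2 and 3.
- Raw scores with baseline as a time level: the group-by-time contrast of post-treatment mean against baseline is the change-score comparison.
- Post-treatment scores only: baseline is not used.

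**Step 2. SDS and SAS (one pre, one post).** Variance per patient is 2(1 − r) for change, 1 for post-only and 1 − r² for baseline-adjusted.
- Adjusted / change = (1 − r²) / [2(1 − r)] = (1 + r)/2 = 0.65, 0.75, 0.85, so variance is 35%, 25% or 15% lower.
- Adjusted / post-only = 1 − r² = 0.91, 0.75, 0.51, so variance is 9%, 25% or 49% lower.

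A simulation with 64 patients per arm and 4,000 runs gave adjusted/change ratios of 0.66, 0.74 and 0.86, in agreement with the formula.

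**Step 3. VAS (mean of three post-treatment cycles).** The variance of the post-treatment mean is (1 + 2r)/3.

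With three baseline cycles averaged, change = 2(1 − r)/3 and adjusted = (1 + 2r)/3 − 3r²/(1 + 2r).

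| r | Change | Adjusted | Ratio | Reduction |
|---|---|---|---|---|
| 0.3 | 0.467 | 0.365 | 0.781 | 22% |
| 0.5 | 0.333 | 0.292 | 0.875 | 12.5% |
| 0.7 | 0.200 | 0.188 | 0.938 | 6% |

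With one baseline value, change = 1 + (1 + 2r)/3 − 2r and adjusted = (1 + 2r)/3 − r².

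| r | Change | Adjusted | Ratio | Reduction |
|---|---|---|---|---|
| 0.3 | 0.933 | 0.443 | 0.475 | 52.5% |
| 0.5 | 0.667 | 0.417 | 0.625 | 37.5% |
| 0.7 | 0.400 | 0.310 | 0.775 | 22.5% |

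Against a post-only analysis, the ratio is 0.684, 0.437 or 0.234 with three baseline cycles, and 0.831, 0.625 or 0.388 with one.

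**Step 4. In practical terms.** Interval width scales with the square root of the variance. For SDS and SAS, √0.65 = 0.81, √0.75 = 0.87 and √0.85 = 0.92, so intervals are about 19%, 13% or 8% narrower than with change scores. For VAS with three baseline cycles, √0.781 = 0.88, √0.875 = 0.94 and √0.938 = 0.97, about 12%, 6% or 3% narrower.

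**Step 5. If the SDs differ.** The excess variance of change scores over adjustment is (b − 1)² times the baseline variance, where b is the slope of post on pre. It is never negative and vanishes only at b = 1. Entry requires VAS above 40 mm, which may narrow the baseline spread; at a fixed slope, that makes the loss smaller.

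**The case against.** The strongest reply is that nothing here is wrong as written. The article is condensed and a separate analysis plan may exist. The covariate list is open, so baseline adjustment is unnamed rather than excluded. The sentence about differences from baseline governs description, while the test has its own sentence with no stated response. A reader might infer that baseline values enter only by subtraction. The text does not support that: it does not say that differences are what the ANOVA analyses, and it also uses baseline data to check balance.

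These points stand and limit the claim. They do not remove it. The document itself fixes the test and gives examples for the covariance model. An open list does not commit the analyst to the most useful covariate and leaves the choice until the data are seen. The unspecified response does not help either, since each reading in Step 1 is less precise than adjustment. Balance testing recovers no precision.

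Three further inferences would go too far.

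- **That the primary comparison gains.** CMSS has no scheduled baseline, so this change does nothing for it. Its missing baseline and its sample size are separate matters and lend no weight here.
- **That the results would be biased.** Under randomisation a change-score comparison is unbiased over repeated samples; what it loses is efficiency.
- **That the VAS gain must be large.** Three baseline VAS scores are not assured: Table 2 has one baseline column and one inclusion column, and the three-cycle run-in is described through the diary. If three are averaged, the gain over change scores may be as small as 6%.

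**Conclusion.** The point holds as an inexpensive improvement to the analysis of VAS, SDS and SAS. The plan collects their baseline values and intends covariance analysis, but does not name those values as covariates. With equal SDs and r between 0.3 and 0.7, adjustment reduces variance relative to change scores by 15% to 35% for SDS and SAS. For VAS the reduction is 6% to 22% with three averaged baseline cycles, or 22.5% to 52.5% with one. Relative to a post-only analysis the gain grows with r instead of shrinking. The direction rests on a general result; the size rests on correlations and SDs that the document does not give. The gain is one of efficiency, confined to secondary outcomes.

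**What to change.** In the Analysis section, add to the covariate sentence that the between-group model for post-randomisation VAS, SDS and SAS scores will include the baseline value of the same outcome as a prespecified covariate. For VAS, use the mean of the available baseline scores. State that adjusted group differences will be reported with 95% confidence intervals. Age, age at menarche and duration of disease may stay as additional covariates.

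The cost is a sentence of text and minor programming. No new data, visits or patients are needed for these three outcomes.
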